## Abstract

**Background:**

Chronic Fatigue Syndrome (CFS) is increasingly recognized as a cause of disability and inactivity in adolescents in the Netherlands. CFS is characterized by unexplained fatigue lasting more than 6 months. Cognitive Behavioural Therapy (CBT) has proven to be effective. However, CBT availability for adolescents with CFS is limited and requires special therapeutic skills not always readily available. An alternative to the face-to-face CBT is FITNET, a web-based therapeutic program designed specifically for adolescents diagnosed with CFS, and their parents. This new CBT approach appeals to the modern youth, who grow up with internet as their main source of information. A web-based program offers the opportunity to lower thresholds for the acceptance and realization of healthcare. This treatment can be activated at any chosen time. The communication between patient and therapist can elapse asynchronously. If effective, this web-based program would greatly increase the therapeutic accessibility.

**Methods/Design:**

A randomized clinical trial is currently conducted. One-hundred-forty adolescents aged 12-18 years diagnosed with CFS will be recruited and randomized to one of two groups: FITNET or usual care. After 6 months, the usual care group will have access to the FITNET program. Outcomes will be assessed at baseline, post intervention, and at 6 months follow-up. Primary outcome measures are school presence, fatigue severity, and physical functioning.

**Discussion:**

The FITNET study is the first randomized clinical trial which evaluates the effect of web-based CBT versus usual care in adolescents with CFS. The intervention is based on a theoretical existing model of CBT for patients with CFS. The results of this study will provide information about the possibility and efficacy of web-based CBT for adolescents with CFS and will reveal predictors of efficacy.

**Trial registration:**

ISRCTN: ISRCTN59878666 and ClinicalTrials.gov: NCT00893438

## Background

Chronic fatigue syndrome (CFS, also known as myalgic encephalomyelitis/encephalopathy or ME) is a disabling disorder, characterized by persistent or relapsing severe fatigue that is not the result of an organic disease or ongoing exertion and is not alleviated by rest. Symptoms last for at least 6 months and are accompanied by other symptoms like muscle pain and concentration problems[1].

The cause of CFS is still unknown. CFS is explained in terms of a central neurobiological disturbance with triggering, sustaining and perpetuating factors both on a biological and psychosocial level[2]. Cognitions concerning these sustaining and perpetuating factors are subject of the cognitive behavioural therapy (CBT) regimen for adolescents. CBT is the only evidence-based treatment with a recovery rate of 70% directly after treatment[3]. An uncontrolled study of the efficacy of family cognitive behaviour therapy for adolescents with CFS, revealed even better results with a recovery rate of 83%, with a maintained gain at 6 months follow-up[4]. However, the availability of this treatment in the Netherlands is limited and it requires special therapeutic skills that are not always readily available.

Furthermore, not all cases of CFS are adequately recognised, neither by the patient nor by their doctor. A large population study in the Netherlands revealed a prevalence rate of 16.4% of severe fatigue lasting more than one month in adolescent girls[5]. The proportion of undiagnosed cases of CFS among these girls is unclear. The lack of treatment possibilities within reach may enhance the reticence in diagnosing CFS.

Although untreated CFS in adolescents has a better prognosis than in adults, the risk of disruption of development and education asks for a prompt recognition of the syndrome and an effective treatment method[3,6]. The longest follow-up study, covering a 13 year follow-up period, showed that the majority of adolescents have mild to moderate persisting symptoms with a considerable period of school absence[6].

The lack of skilled cognitive behavioural therapists to treat adolescents with CFS made us decide to develop a web-based application combing CBT by a skilled therapist with a regular internet contact. In a recently published non-inferiority randomised controlled trial (RCT) by the Expert Centre for Chronic Fatigue (ECCF) in Nijmegen, a minimal intervention based on CBT for CFS, consisting of a self help booklet (workbook) supported by email contact with a cognitive behavioural therapist, appeared to be effective[7]. This Self Help Program resembles a web-based CBT in certain aspects, such as the absence of face-to-face contact between therapist and patient. However, in the minimal intervention study the contact between therapist and patient was minimal, whereas in the web-based CBT there will be frequent email contact between therapist and patient.

Web-based CBT for illnesses other than CFS has been found effective, but most research has been conducted with adults[8,9]. For adolescents, web-based CBT has been developed for disorders such as obesity [10], depression [11], anxiety [12], headache [13] and smoking cessation [14]. The efficacy of these web-based CBT programs in general is comparable with the face-to-face treatments[8,9,13,15].

FITNET (web-based treatment for Fatigue In Teenagers) is a Dutch web-based program developed in close collaboration between the Wilhelmina Children's Hospital (University Medical Centre Utrecht, UMCU) and the Expert Centre for Chronic Fatigue (Radboud University Nijmegen Medical Centre, ECCF). FITNET is a highly structured program for adolescents with CFS and consists of two parts: a psycho-educational part for both adolescents and parents and a CBT part based on the protocol of the ECCF[16]. The efficacy of this protocol in a face-to-face setting for adolescents has been demonstrated in a randomized controlled trial[3].

The primary aim of this study is to determine the efficacy of FITNET for adolescents with CFS in the Netherlands. The second goal of this study is to explore predictors of outcome.

## Methods/Design

### Study design

A single-blinded randomized clinical trial (RCT) with 6 months follow-up will be conducted to evaluate the efficacy of FITNET compared to usual care for adolescents with CFS. Efficacy of FITNET compared to usual care will be determined after 6 months, the maximum duration of the treatment. Patients assigned to FITNET have to agree to not have any further medical examinations or other treatments for fatigue whilst in therapy[17]. The adolescents who have been assigned to the usual care will get the opportunity to attend the program after these 6 months. The total follow-up time is 12 months after the start of the web-based program. (*see Figure *1).

**Figure 1 F1:**
[figure not shown]
Flowchart of trial design.

CFS will be diagnosed after a uniform diagnostic work-up by a paediatrician specialised in CFS (EP), according to CDC-criteria[1]. Once the diagnosis is established, study eligibility will be assessed by completing self-reported questionnaires on fatigue, physical complaints, physical functioning, depression and anxiety. Eligible patients will be asked to participate in this RCT. If the patient is willing to participate, the primary investigator (SN) will check the inclusion and exclusion criteria (*table *1). When a patient meets all criteria, oral and written consent will be obtained from both patient and at least one parent, according to the declaration of Helsinki. The patients with a possible psychiatric comorbidity and their parents will be examined by an experienced child psychologist before randomisation. Patients with a primary psychiatric diagnosis, as assessed by this psychologist, will be excluded from the trial. If the adolescent or the parent(s) decide not to participate in the study, the reason will be asked and specified, although they are not obligated to reveal such reasons. During the intervention we expect some adolescents to drop-out. The reason to stop will be asked and specified.

**Table 1 T1:** Inclusion and exclusion criteria

Inclusion criteria
(1) The participant has given written informed consent

(2) CFS diagnosis according to the CDC criteria [1]

(3) Adolescent between 12-18 years old at inclusion

(4) Fatigue severity subscale (CIS-20) score ≥40 (healthy population's mean plus two SD) [19]

(5) Physical functioning (Child Health Questionnaire) score <85 (healthy population's mean minus two SD) and/or school participation ≤85% (healthy population's mean minus two SD) in last two weeks [20]

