### Randomization and blinding

Concealed randomisation will be performed by the data-management section of the Julius Centre for Health Sciences and Primary Care Utrecht. This randomization is computer-generated by creating 'blocks' with a size of 6, ensuring that the same number of participants will be allocated to each group. The investigators who are responsible for the inclusion will be blinded. Primary outcome parameters will be assessed by computer.

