**Primary outcome parameters**					

Fatigue severity	Checklist Individual Strength (CIS subscale fatigue) [19]	X	X	X	X

Physical Functioning	Child Health Questionnaire (CHQ-CF87 subscale physical functioning) [20]	X	X	X	X

School presence	Last two weeks school presence expressed in attended hours/obliged hours * 100%[3]	X	X	X	X

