### Power

We estimate that under care as usual the estimated average percentages of school absence, our primary endpoint, at the end of follow-up, will be 40%. Given the efficacy of face to face CBT in adolescence [3] we consider a reduction of school absence of 15% in the e-intervention group to be realistic and highly relevant. In order to statistically detect such a reduction, given a 2 sided-alpha of 0.05 and with 90% power, we will need to allocate 60 patients to each group. In order to accommodate a small anticipated percentage of non-participation we will include 140 diagnosed patients.

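### School presence at entry is known before allocation and bears on the endpoint that sizes the trial, yet it is neither a stratification factor nor a fixed covariate

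*Protocol article*

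**What the plan says.** Inclusion criterion 5 (protocol article, Table 1) reads "Physical functioning (Child Health Questionnaire) score <85 (healthy population's mean minus two SD) and/or school participation ≤85" per cent, over the last two weeks. Either limb is enough. Criterion 4 separately requires a fatigue score of at least 40 from everyone.

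Table 2 defines the outcome as "Last two weeks school presence expressed in attended hours/obliged hours * 100" per cent, measured from T0 onwards. It is one of three primary outcomes, with fatigue severity and physical functioning.

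The Power section sizes the trial on this outcome alone. It assumes that "under care as usual the estimated average percentages of school absence, our primary endpoint, at the end of follow-up, will be 40" per cent, and states that "we consider a reduction of school absence of 15% in the e-intervention group to be realistic and highly relevant". It continues: "given a 2 sided-alpha of 0.05 and with 90% power, we will need to allocate 60 patients to each group". The total is then raised: "In order to accommodate a small anticipated percentage of non-participation we will include 140 diagnosed patients".

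On allocation, the Randomization and blinding section says: "This randomization is computer-generated by creating 'blocks' with a size of 6, ensuring that the same number of participants will be allocated to each group". It names no stratification factor.

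The Statistical Analysis section plans an intention-to-treat comparison at 6 months and a table of prognostically important baseline characteristics. Regression adjustment comes on top of the main comparison, and only where the groups differ in prognosis at baseline. Baseline school presence is not named there.

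**The concern.** Criterion 5 produces two kinds of patient with respect to school presence. Some enter with substantial absence. Others enter with more than 85% presence, which the protocol's own label places within two SD of the healthy mean, and have little room to improve on this outcome. The two kinds are likely to differ widely in presence at 6 months whatever the treatment, so entry school presence should be a strong prognostic factor for the endpoint that sets the sample size.

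That factor is checked for eligibility and is therefore known before allocation. If it is left out of both the allocation and the main analysis, the spread between the two kinds of patient stays in the standard error, and a chance surplus in one arm moves the estimate. An adjustment made only when an imbalance is noticed depends on a judgement taken after the baseline data are seen, and it leaves two estimates, adjusted and unadjusted, with different precision.

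**Working it through.** **1. Room to improve.** Room = 100 − presence at entry. At 85% it is 15 points, above 85% it is less than 15, and at 100% it is zero. This takes the 15% as absolute points (40% to 25% absence). A relative reading would be 0.15 × 40 = 6 points.

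**2. The plan's figure of 60 per group.** No SD is stated, so it has to be solved for. From n = 2 × [SD × (1.960 + 1.282) / 15]², n = 60 gives SD = 15 × √30 / 3.242 ≈ 25.3 points. An SD of 25 gives 59 per group, 30 gives 85 and 35 gives 115. Comparing 40% with 25% as two proportions needs 203 per group, so the means reading is the one that fits. On the relative reading, 60 per group would need an SD of about 10.1. The recruitment allowance is 1 − 120/140 = 14.3%.

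**3. What unused baseline information costs.** Let f be the share entering above 85%, and D the difference in mean presence at 6 months between the two kinds of patient. Neither is in the documents, so both are assumed. The variance between the two kinds is f(1 − f)D². Using the stratum in the analysis removes it from the total of 25.35² = 642.4, so the standard error falls by the fraction 1 − √(1 − f(1 − f)D²/642.4).

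| f | D = 20 | D = 30 | D = 40 |
|---|---|---|---|
| 10% | 3% | 7% | 12% |
| 20% | 5% | 12% | 22% |
| 30% | 7% | 16% | 31% |

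Example: f = 20%, D = 30 gives 0.16 × 900 = 144, then 144/642.4 = 0.224, and 1 − √0.776 = 12%.

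**4. Chance imbalance in the share.** The 95% range for the difference in f between arms is ±1.96 × √(2f(1 − f)/n), ignoring the small effect of blocking. At 70 per arm this is about ±10 percentage points for f = 10%, ±13 for 20% and ±15 for 30%. Multiplying by D gives its effect on the estimate. At f = 20% and D = 40 it is 0.133 × 40 ≈ ±5 points of school presence, against a target of 15. This is the same variation as in step 3, seen in a single trial, and not an additional loss.

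**5. Dilution of the average effect, for scale.** Suppose the effect is 15 points in patients at or below 85% and g in the rest. The average is then 15(1 − f) + gf. With SD 25.3 and 60 per arm:

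| f | Average, g = 0 | Power | Average, g = 7.5 | Power |
|---|---|---|---|---|
| 10% | 13.5 | 83% | 14.25 | 87% |
| 20% | 12.0 | 74% | 13.5 | 83% |
| 30% | 10.5 | 62% | 12.75 | 79% |

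These figures hold only if the 15 points is taken to belong to the absent pupils alone, which the Power section does not say.

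**The case against.** A reader might infer that patients above 85% put the 15-point target out of reach. The text does not support that. The Power section compares average absence between arms at the end of follow-up; it does not require any single patient to gain 15 points. Its averages describe the trial population and may already include near-ceiling entrants. A 15-point average remains possible with no effect at all in those patients, if the others differ by 15/0.9 = 16.7 points at f = 10% or 15/0.8 = 18.8 at f = 20%. Near-ceiling patients can also contribute by worsening less than they would under usual care.

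A reader might also infer that randomisation fails to balance these patients. It balances them in expectation. What remains is chance imbalance, which the confidence interval covers, and the Statistical Analysis section offers an adjustment. Both objections stand.

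The criterion itself is coherent. A patient admitted on physical functioning below 85 also has fatigue of at least 40, and so is impaired on the other two primary outcomes. An assumed average absence of 40% under usual care suggests that most patients are well below the ceiling.

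Finally, the article is a condensed text, and a fuller document might name a stratification factor. That limits the point without removing it. The article does state how allocation is done, and it does fix a conditional rule for adjustment. That rule is a choice made in the text and can be judged as one.

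**Conclusion.** The point holds as a modest, inexpensive improvement in efficiency. It does not show a biased comparison, a wrong entry rule or an unattainable target. Three facts carry it: criterion 5 admits patients above 85%, school absence alone sets the sample size, and neither the allocation nor the main analysis described makes fixed use of school presence at entry.

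The gain is a standard error smaller by about 3 to 31%, for f between 10 and 30% and D between 20 and 40 points. It rests on a back-solved SD and on a share and a difference that the documents do not give. The dilution figures depend on a reading of the target that the text does not state, so they should not be cited as the trial's power.

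**What to change.** - Keep criterion 5, and keep the all-randomised comparison as the main analysis.
- Stratify the computer-generated allocation by T0 school participation, ≤85% or >85%, using the value already checked for eligibility.
- Always include T0 school presence, or the stratum, in the linear regression for school presence, whether or not an imbalance is seen. If the allocation can no longer be changed, this step alone brings most of the benefit.
- The effect in the ≤85% stratum may be reported as a supportive estimate. The 15-point target should not be moved to it. With SD 25.3 and a 15-point effect there, 54, 48 or 42 patients per arm (f = 10, 20 or 30%) give only about 87, 83 or 77% power, and a second reading of a primary outcome would need a rule for conflicting results.

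The cost is one binary factor in the existing randomisation system and one covariate. With blocks of 6, an unfinished last block can leave the arms unequal by at most 3 patients in each stratum. The benefit may be small if few patients enter above 85%.

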**Exclusion criteria**

(1) Inadequate control of Dutch language by child or parent

(2) No availability of computer hardware and internet connection

(3) Suicide risk as assessed on the Children's Depression Inventory (CDI) [21]

(4) Cognitive retardation (when indicated an IQ-test will be conducted; IQ <85 will be excluded)

(5) Score greater than or equal to 44 (healthy population's mean plus two SD) on the State-Trait Anxiety Inventory for Children (STAIC) [23]

(6) Score greater than or equal to 16 (healthy population's mean minus two SD) on the Children's Depression Inventory (CDI) [21]

### Study population

It is intended to include 140 adolescents aged 12-18 years old, referred to the University Medical Centre Utrecht (UMCU) and diagnosed with CFS using the CDC-criteria[1].

The patients will be recruited from second-line medical care by means of the National Surveillance Centre for Children (NSCK), which is part of the International Network of Pediatric Surveillance Units, INoPSU[18]. The NSCK survey guarantees a high percentage of reporting (83-92%) of the diagnosis under consideration. Recruitment from primary care will be realised by announcement of this study to all General Practitioners in the Netherlands (with help of the NIVEL, the Dutch Collaborating Centre of the WHO). In addition, on the website of the 'CVS-ME Stichting' (a Dutch CFS Foundation) a direct call to participate in this study will be published.

### Ethical approval

This study has been reviewed and approved by the Medical Ethical Committee of the University Medical Centre Utrecht (reference 07/196-K) and the Medical Ethical Committee of the Radboud University Nijmegen Medical Centre (reference AMO nr. 07/105). Patients and their parents receive verbal and written information about the study and informed consent will be obtained before randomisation.

### Randomization and blinding

Concealed randomisation will be performed by the data-management section of the Julius Centre for Health Sciences and Primary Care Utrecht. This randomization is computer-generated by creating 'blocks' with a size of 6, ensuring that the same number of participants will be allocated to each group. The investigators who are responsible for the inclusion will be blinded. Primary outcome parameters will be assessed by computer.

### Interventions

#### Usual care

The patients in the control group will receive the usual care available in the region where the patient lives. The available usual care for adolescents with CFS in the Netherlands includes: individual/group based rehabilitation programs, psychological support including CBT face-to-face, graded exercise therapy by a physiotherapist, etc. All care received will be monitored during the study.

#### Web-based Cognitive Behavioural Therapy (FITNET)

FITNET is a web-based cognitive-behavioural treatment accessible to patients and both parents, based on the existing face-to-face CBT protocol for adolescents developed by the ECCF [3,17]. Trained cognitive behavioural psychotherapists from the ECCF will support the patients by e-consults. There will be no face-to-face contact between the therapists and patients at all.

The web portal is designed by the UMCU in collaboration with the ECCF, and has been developed in cooperation with adolescents with CFS who critically appraised text, lay-out and structure. Two authors of children books ([name]) revised the textual content on readability for adolescents. All therapists receive a special half a day training in the application of written language for this target group.

The programme consists of a psycho-educational and a CBT section. The psycho-educational section will be readily available, after receiving log in codes. The CBT section consists of 21 interactive modules (*see appendix 1*), accessible upon activation by the therapist. The web-based therapy comprises about 20 internet-sessions over 6 months. Meanwhile, the parents will follow a parallel program. All users will have a unique username and password, ensuring private communication with the therapist. Both parents and adolescents will have a regular e-consult (email contact) with the therapist, wherein results so far are discussed and new assignments can be given. The therapist will reply on a fixed weekday. The patient will have the ability to send an emergency email, on which a prompt reply will be made. For emergency situations, telephone contact details are available for the patient.

The FITNET treatment programme is implemented in a portal with a lay-out especially designed for adolescents, combining different applications such as: e-consult, personal diaries, questionnaires, psycho-education, all treatment steps and the possibility to review previous communications and assignments. Patient data and emails will be encrypted and securely stored on the UMCU mainframes to guarantee privacy and confidentiality. The treatment protocol is described in more detail in the appendix.

### Compliance and attrition

Therapy compliance will be assessed by recording the number of treatment-modules (CBT) that have been completed. When applicable, participants will be asked for their reasons for poor compliance. In the case of therapy drop-out, patients will be asked for the reason of non compliance and stimulated to continue participation in the assessments until the last follow-up.

